#### Secondary outcome measures

Change in quantity (in mass) and waste composition at different time points in the study when compared with the baseline between the intervention and control groups as assessed by pick analysisComparison of change in knowledge and practices about solid waste management at household level at different study time points when compared to the baseline between the intervention and control group (assessed by *Waste segregation knowledge, behaviour questionnaire)*

### Study tools

*Pick analysis (waste composition assessment): *Pick analysis is a method to characterize the content of a waste stream. This analysis aims to estimate the waste generation per capita per time and to analyse waste segregation behaviour where waste fractions were sorted correctly based on the recycling schemes. This method can measure the actual waste sorting behaviour at household/community level. The method was developed and validated by Dahlén and Lagerkvist [34] and is a recommended method by Swedish Waste Management Association [35](2013). Rousta et al. (2016) have implemented this method to create RBT procedure (Recycling behaviour Transition) to design and assess the interventions of increasing the recycling rate of a community in a medium-sized city [31]. A pre- designed proforma to capture the quantity and composition of the waste generated at group level will be used.*Waste segregation knowledge, behaviour questionnaire***:** Based on the literature [11, 13, 22, 36–41] and experts’ consultation, the research team has developed an extensive questionnaire to assess the awareness, attitude and behaviour related to household level waste segregation. This questionnaire will be used to assess the belief, social norms, knowledge, ability, motivation factors, opportunity and practices about waste segregation study household members. One section of the questionnaire will capture socio-demographic details of the study households.*Intervention log-book (Volunteer log book):* A pre-designed log book will be used by the volunteers to monitor the attendance of household members present during intervention and any other information shared by household members.

### Testing and validation of study tools

All assessment questionnaires will be validated using face and content validation method for comprehensibility, simplicity, relevance and cultural acceptability. Pretesting of the study tools will be done with randomly selected households (*n* = 30–50) not part of the trial to assess the overall feasibility of the proposed intervention, improve the intervention implementation, and inform the design of a tailored intervention.

### Assessments (Table 1)

Assessment will be conducted at four time points (baseline, midline, end line and post intervention) across the study period.
*Baseline: *At baseline, all the households (intervention and control group households) will be assessed for the following:
○ Waste composition assessment through pick analysis, which is a reliable and validated method to assess the composition of the waste generated at group level.○ General socio-demographic details and waste segregation knowledge and behaviour.Findings of waste composition at baseline will be shared with respective households and two dustbins will be provided to each household (intervention and control) with relevant information regarding waste segregation.*Midline: *At the halfway point of the intervention (6th month), waste composition analysis of all the households (intervention and control group households) will be conducted using the pick analysis method.*End line:* At the 12^th ^intervention month waste composition, waste segregation knowledge and behaviour will be assessed again using the same methods as in the baseline assessment.*Post Intervention ***:** Waste composition, waste segregation knowledge and behaviour will be assessed finally at the 18 month mark (6 months after intervention completion). Feedback about the intervention will be collected from participants at this assessment.

**Table 1 Tab1:** Assessment plan

Time Point	Baseline (M-0)		Intervention period (12 Months)				Post Intervention (M-18)	
			Midline (M-6)		End line (M-12)			
Study tools	Intervention	Control	Intervention	Control	Intervention	Control	Intervention	Control
Socio-demographic	X	X	–	–	–	–	–	–
Waste composition analysis	X	X	X	X	X	X	X	X
Knowledge and behaviour, about waste segregation	X	X	–	–	X	X	X	X

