### Blinding

As the intervention consists of training that targets a change in behaviour, blinding of the study participants and investigators is not possible. However, the study team responsible for conducting outcome assessments will be blinded in terms of the households’ allotted groups and the participants will be requested to not discuss their allocation with the research team responsible for conducting follow-up assessments in order to minimize bias.

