**Fortnight visit for I-MISS Intervention**								

### Intervention fidelity

Standard operating procedure (SOPs) will be prepared, to ensure a standard intervention package in all intervention households. Adequate induction and refresher trainings for volunteers in all aspects of intervention content and for SOPs will be conducted. Participating households in the intervention arm will be contacted telephonically monthly by a separate team (not involved in outcome assessments) to get feedback about the intervention delivery by the volunteers and to ensure visits have been conducted. The investigators will conduct a monthly meeting with the volunteers to collect their feedback on the trial process and implementation*.*

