### Methodological Considerations

The project is built on the interdisciplinary strengths of the teams in the Sweden and India. Leveraging each team’s complementary intellectual contribution whilst providing opportunities for learning and capacity building across the teams is one of the strengths of the study. Adoption of behaviour change theory and multiple methods to develop the intervention is considered as one of the strengths of the study. The adoption of sound study design (c- RCT) as per CONSORT guidelines [23] and comprehensive sampling strategy with adequate sample size will lead to generate high level evidence which could be extrapolated to population level.

The study households /participants will not be blinded regarding the group they were allocated. This could exaggerate the difference in outcomes measurement between the two groups. Also, the attention given to intervention participants during home visits by volunteers, in itself may raise adherence (through the Hawthorne effect). Although volunteers will ensure that all household members should participate in fortnightly session, it is possible that some household members will not be there for these sessions. Errors may be made while measuring waste fraction during waste composition study. To minimize uncertainty in the data collection, all waste composition measurements at different time points will be conducted in presence of senior project staff with the same supporting staff. The same measuring equipment and protocol will be followed in all measurement sessions.

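### Collecting feedback on the intervention at the month-18 outcome assessment conflicts with the stated assessor blinding at that time point

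*Protocol article*

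**What the plan says.** All references are to the protocol article.

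- **Blinding.** The section states that "blinding of the study participants and investigators is not possible", but that "the study team responsible for conducting outcome assessments will be blinded". To support this, participants will be "requested to not discuss their allocation with the research team responsible for conducting follow-up assessments".
- **Assessments (Table 1), post-intervention.** "Waste composition, waste segregation knowledge and behaviour will be assessed finally at the 18 month mark", six months after the intervention ends. The next sentence reads: "Feedback about the intervention will be collected from participants at this assessment". It does not say who collects the feedback, or whether this comes before or after the outcome measures.
- **Intervention fidelity.** While the intervention runs, intervention households are telephoned monthly about its delivery by a team kept apart from outcome measurement.
- **Study design and Sampling strategy.** Wards are the unit of allocation. Eight wards in four pairs are used, one ward of each pair going to each arm, with about 110 households recruited per ward.
- **Primary outcome measures.** The first is self-reported segregation, taken from the household questionnaire. The second is the proportion of mis-sorted waste, measured at group level by pick analysis.

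**The concern.** The plan relies on participants keeping quiet about their arm when they meet the assessors, and then schedules a conversation about the intervention at an outcome assessment. Feedback on the intervention discloses the arm however it is organised. If only intervention households are asked, the presence of the feedback form is enough. If all households are asked, the answer shows whether a volunteer has been visiting.

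Month 18 is the only assessment made after the volunteers stop. The Background names keeping up changed behaviour as the main difficulty in this field, so this is the time point that speaks to durability. It is also one of only two post-baseline measurements of the self-reported outcome. Participants know their arm, and Methodological Considerations accepts that this could inflate the difference between groups. Blinding of the person asking the questions is a partial protection for a self-reported outcome, but it is one that the plan claims and should keep.

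**Working it through.** No sample size, power or error rate is involved, so there is no figure of the plan's to reproduce. The check sets the sections side by side and counts what one disclosure reveals.

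**1. Compatibility at month 18.** Blinding requires that the follow-up team does not hear the allocation. The Assessments section places feedback on the intervention at the follow-up assessment itself. Both can hold only if someone else collects the feedback, or if it comes after the outcome data it could influence. Neither condition is stated. Intervention fidelity does state the first condition for the monthly calls during the intervention, but nothing extends it to month 18.

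**2. What one answer reveals.** Inputs from Sampling strategy: 5 groups × 22 households = 110 per ward; 4 wards per arm; 8 wards in 4 pairs.

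- One household's feedback reveals its ward: about 110 recruited households.
- Within a pair the arms are opposite, so anyone who knows the pairing also learns the partner ward: 2 × 110 = 220.
- Four disclosures, one per pair, reveal all eight wards: 8 × 110 = 880.

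These are recruited numbers. With the 20% loss to follow-up allowed for in Sample size, a ward would have about 110 × 0.80 = 88 households at month 18.

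**3. Would asking for feedback last in each visit be enough?** Suppose the same assessors take both outcomes and feedback. With one assessor in a ward, only the first household is assessed blind, and 110 − 1 = 109 are not. With five assessors who do not talk to each other (an illustrative number, one per group of 22), five households are assessed blind and 110 − 5 = 105 are not, about 95%. The order of questions within a visit therefore does not solve the problem. The order across the ward does, as does a different collector.

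**4. Which measurements can be affected.** From Table 1 and the assessment text:

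| Outcome | Months measured | Exposed to the feedback |
|---|---|---|
| Self-reported segregation | 0, 12, 18 | 18 only |
| Mis-sorted waste (pick analysis) | 0, 6, 12, 18 | 18 only, and only if sorters take or hear the feedback |

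Months 0, 6 and 12 come before the feedback and cannot be touched by it.

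**The case against.** The strongest reply is that the article does not say who collects the month-18 feedback or when. A separate team, or collection after the outcome data, is not excluded. Staffing and the order of items are details that a condensed article may leave to the full protocol or operating procedures, and the monthly calls show that the authors know how to keep the two tasks apart. It can also be said that respondents who know their arm are the larger source of bias in a self-reported outcome, and that the pick analysis is a group-level measurement made with a fixed proforma, equipment and procedure.

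Much of this stands. It rules out saying that blinding has certainly failed, and it limits the effect on the pick analysis to a possibility. It does not remove the conflict. The article prints a claim of blinded assessment and a feedback task at the same assessment, and leaves out there the safeguard it gives elsewhere.

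A reader might go further and infer that the pick analyses are unblinded at every follow-up, because "all waste composition measurements at different time points will be conducted in presence of senior project staff with the same supporting staff", investigators cannot be blinded, and "The investigators will conduct a monthly meeting with the volunteers to collect their feedback on the trial process and implementation". The document does not support that chain. It never says that the senior staff are investigators, that they meet volunteers or that they know the allocation, and it gives their presence as a control on measurement error. The most that can be asked is a statement of whether those attending know the allocation.

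**Conclusion.** The concern holds, limited to month 18. As written, collecting feedback on the intervention at that assessment conflicts with the claim that assessors are blinded, and allocation by ward turns one disclosure into knowledge of about 110 recruited households. The main exposure is the self-reported primary outcome at one of its two post-baseline measurements, the only one after the intervention ends. Exposure of the pick analysis is conditional on shared staff or shared information.

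This rests on two assumptions that the article neither states nor excludes: that the outcome assessors take the feedback or learn of it, and that the questionnaire is administered by those assessors. The amount of bias cannot be derived from the document. A bias towards the intervention is plausible but not shown.

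A reader might infer that assessor blinding is undone throughout the trial. That does not follow, because the assessments at months 0, 6 and 12 precede the feedback.

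**What to change.** Take intervention feedback out of the month-18 outcome visit. Assign it to the telephone team already described under Intervention fidelity, to be collected after all month-18 outcome data for the ward, both questionnaire and pick analysis, are recorded. Waiting until all eight wards are complete is better, because the paired allocation lets one ward reveal its partner. Amend the post-intervention paragraph of Assessments to say so, with a cross-reference to Blinding.

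Separately, add one sentence under Blinding stating whether the senior staff present at the pick analyses know the allocation. This is a clarification only.

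The cost is a slightly later feedback contact. The team already exists, and neither the design, the sample size nor the outcome schedule changes.

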**Fortnight visit for I-MISS Intervention**								

### Intervention fidelity

Standard operating procedure (SOPs) will be prepared, to ensure a standard intervention package in all intervention households. Adequate induction and refresher trainings for volunteers in all aspects of intervention content and for SOPs will be conducted. Participating households in the intervention arm will be contacted telephonically monthly by a separate team (not involved in outcome assessments) to get feedback about the intervention delivery by the volunteers and to ensure visits have been conducted. The investigators will conduct a monthly meeting with the volunteers to collect their feedback on the trial process and implementation*.*

### Loss to Follow-Up

Where households are not available for assessments the project team will make multiple (approximately 5) attempts to contact the head of household or primary/secondary member responsible for waste disposal or any members of the household to reschedule the missed visit. The investigator will ensure every effort to regain contact with the household before classifying a household as lost to follow up. These contact attempts will be documented in the trial record. Thus, if the team fails to make contact of the households after 5 attempts or if the household respondents revoke the consent to participate in the study will be labelled as lost to follow up.

### Ethical Considerations and approvals

The study is approved by the institutional ethics committee of ICMR-National Institute for Research in Environmental Health, Bhopal (No. NIREH/BPL/IEC/2020–21/41, dated 21st April, 2020) and R.D. Gardi Medical College, Ujjain (No.03/2020, dated March 12th 2020). The study is approved by Health Ministry Screening Committee (2020/9308). The study is prospectively registered in Clinical Trials Registry India (CTRI/2020/03/024278).

Written informed consent will be obtained from all participants. Households will be given the option to withdraw from the study at any time without justification. If the household decides to withdraw from the study, the research team may keep and continue to use any data collected before the withdrawal. However, if a household withdraws from the trial, they may request destruction of any data collected.

The objective of this trial is to assess the change in waste segregation practice using volunteer based improved information which are not anticipated to cause any adverse events or risk to participating households. However, study or follow-up assessments may create additional stress of segregating waste, but unlikely to such an extent that it will cause harm. We anticipate no or less than minimal psychological discomfort related to waste segregation activities and frequent home visits made by project staff. Each visit will be done at convenient time for the study participants. Only interested participants will be involved in the study. All ethical procedures will be followed across the study period.

Data confidentiality will be guaranteed through well-established protocols for data collection and processing. Unique identifier will be assigned to participants. The key linking the personal data with related results will be kept inside locked cabinets and shall be accessed only by the authorized staff. Paper-based forms will be filled to document epidemiological data (e.g. socio-demographics and other information). These forms will be kept under the custody of the authorized in-charge manager and subsequently entered in electronic database. Hard copies of all the data collection forms will be stored in a locked archive with restricted access. Electronic data will be stored in password-protected computers in restricted working areas accessible to project staff only. Incremental back-up files will be produced weekly. Any participant records or datasets that are transferred to other participating institute will contain the identifier only; participant names or any information which would make the participant identifiable will not be transferred. The results of proposed trial will be disseminated through community presentations, workshops, policy briefs, in meetings, in conferences and through publications in peer-reviewed journals. Any amendments in the approved proposal during implementation will be communicated to all the institutional ethics committees of participating institutes.

### Strategies to Maintain Adherence

To reduce participant attrition, an initial face to face information session among participant households will be conducted prior to the project start. The project team will inform participants about the study objectives and address queries and concerns. Participants will be contacted monthly for their feedback and also to address their queries and concerns.

### Community Advisory Board

A community advisory board (CAB) will be setup. The board will comprise of waste management professionals, community members and academicswho will hold dialogue with the study participants about the study. CAB members will also give feedback to the project team.

### Database management

The principal investigator will oversee the process of data management. REDCap will be used for database management. Participants will be given a unique participation information number (PIN) to ensure anonymity and data confidentiality. The entered data will be analysed using to appropriate statistical software. Descriptive statistics will include the mean, median, standard deviation and Interquartile range to summarize the numerical variables. Frequencies and percentages will be used for the categorical variables. Student t test will be used to compare means between the groups and chi square test will be used to compare the percentages between the groups. For skewed data, appropriate non parametric tests will be used. ANOVA repeated measures will be used to compare the means across the study periods (multiple time points) within the groups. Factorial ANOVA will be used to compare the means between the groups across the study period (multiple time points). Appropriate post hoc test (Bonferroni test) will be applied. Multi-level modelling (MLM) and Generalized Estimating Equation (GEE) will be done to adjust the clustering effect and to compare the proportions between the groups across the study period. Intention-to-treat analyses will be followed to assess interventions’ effectiveness.

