##### Sample size

The sample size will be based on the differences in proportion, assuming that 50% households segregate waste in both groups. As we could not find previous literature quantifying the effect of similar kind of intervention in Indian setting, we assumed that in our study the intervention will increase the waste segregation practice in the intervention group by 20% compared to the control group. Given a 5% significance level and 80% power, then the minimum sample size is *n* = 184 per group. Assuming a design effect of 2 to adjust for the clustering effect, with 10% non-response rate and 20% loss to follow-up, the final sample size for each arm will be 425 households (total 850 households).

We have fixed the cluster number as eight. As the required sample size is 850 households, we will recruit 850 households from 8 wards i.e., around 110 households (cluster size) will be recruited from each ward.

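### The between-arm tests named for means (Student t, rank tests, factorial ANOVA) and the chi-square test for percentages have no ward term, and the cluster-adjusted methods are tied by name only to proportions

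*Protocol article*

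**What the plan says.** All references are to the protocol article.

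- **Study design and Sampling strategy:** the ward is the randomised unit. Eight wards are chosen as four pairs matched on slum share, and one ward of each pair goes to each arm.
- **Sample size:** the plan allows for clustering: "Assuming a design effect of 2 to adjust for the clustering effect". About 110 households are recruited per ward.
- **Database management, unadjusted tests:** "Student t test will be used to compare means between the groups and chi square test will be used to compare the percentages". Both tests are meant to compare the arms. The text then adds: "For skewed data, appropriate non parametric tests will be used". Factorial ANOVA is given to means between the groups over the time points. No ward term is mentioned for any of these.
- **Database management, adjusted methods:** one later sentence says that multi-level modelling and GEE "will be done to adjust the clustering effect and to compare the proportions between the groups across the study period".
- **Primary outcome measures:** the first is a self-reported household proportion. The second is the share of mis-sorted waste, measured at group level. Both are defined as a difference between arms in change from baseline.
- **Secondary outcome measures:** these include waste quantity and composition, and knowledge and practices.

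**The concern.** Student t, chi-square, household rank tests and an ordinary factorial ANOVA all treat the units within a ward as independent. With wards randomised they are not independent, and the plan's own sample size says so. The article therefore allows for clustering when it counts households and then names tests that ignore it.

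Two consequences follow from the wording:

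- For means, such as waste quantity or any knowledge score, the only between-arm methods named are unadjusted. Ordinary ward-to-ward variation could then produce a positive secondary finding.
- For the household-segregation proportion, chi-square and MLM/GEE are both named and neither is said to govern. The two can disagree, and the unadjusted one will tend to look more favourable.

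**Working it through.** **Inputs.** The significance level comes from Sample size ("Given a 5% significance level and 80% power"); sidedness is not stated, so two-sided is assumed. The design effect of 2, about 110 households per ward, eight wards, 10% non-response and 20% loss to follow-up come from the same section.

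**The plan's own figures.** The only type I error stated is the nominal 5%. The sample-size figures do not reproduce:

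- Under "assuming that 50% households segregate waste in both groups" and a 20% increase, the usual two-proportion formula (two-sided 5%, 80% power) gives 93 per group for 0.50 vs 0.70 and 388 for 0.50 vs 0.60. The plan states 184.
- From 184, 184 × 2 / 0.9 / 0.8 = 511, against the stated 425.

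That is a separate matter. The error rates below depend only on the significance level and the design effect.

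**Step 1. Error of an unadjusted test.** If the true variance of the arm difference is DE times what the test assumes, the true two-sided error is 2 × [1 − Φ(1.96/√DE)].

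- DE = 1: 5.0%, the nominal value.
- DE = 2: 1.96/1.414 = 1.386, giving 16.6%. Intervals are too narrow by a factor of √2 = 1.41.

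**Step 2. Which cluster size the design effect refers to.** DE = 1 + (m − 1) × ICC.

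- If DE = 2 holds at m = 110, ICC = 1/109 = 0.0092.
- After losses, m = 110 × 0.9 × 0.8 = 79.2, so DE = 1 + 78.2 × 0.0092 = 1.72 and the error is 13.5%.
- The documents give no ICC. For assumed values at m = 79, ICC 0.02 gives DE = 2.56 and 22%; ICC 0.05 gives DE = 4.9 and 38%.

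**Step 3. Simulation check.** Four wards per arm, 110 households per ward, ICC = 1/109, no intervention effect, one visit, no pairing effect; binary outcomes are beta-binomial with p = 0.5.

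| Test at nominal 5% | Rejects |
|---|---|
| Student t on households (normal outcome) | 16.4% |
| Chi-square on households | 16.4% |
| t test on ward proportions, unpaired (6 df) | 5.1% |
| t test on ward proportions, paired (3 df) | 5.1% |
| GEE-type sandwich z test, no small-sample correction | 14.1% |

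**Step 4. Group-level waste outcomes.** This takes group level to mean the groups of 22 households, five per ward, and applies the same household ICC.

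- Group-mean ICC = 0.0092 / (0.0092 + 0.9908/22) = 0.17.
- DE = 1 + 4 × 0.17 = about 1.7, and the error is about 12–13%.

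This is illustrative only, because the design effect was set for a household proportion.

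**The case against.** **The primaries are already covered.** Both primary outcomes are called proportions, and MLM/GEE are named for proportions over the study period. This stands for household segregation. A reader might infer that the trial's main analysis has a 17% error rate; the text does not support that, since the figure belongs to the unadjusted tests only. For mis-sorted waste the position is less clear, because a share of mass averaged over groups could be handled either as a proportion or as a mean.

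**The adjustment may be meant for everything.** The MLM/GEE sentence gives two purposes, and the first, adjusting for clustering, is not expressly limited to proportions. That reading is possible. But the only comparison the sentence names is of proportions, and the sentences before it expressly give means to t tests and ANOVA.

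**Change from baseline is analysed.** A reader might infer that the plan compares only levels at one visit. It does not say so: the group-by-time term of a factorial ANOVA is a difference in change, and MLM/GEE run across the study period. The defect is the missing ward term, not a missing analysis of change.

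**The size may differ.** Change from baseline removes stable ward differences, and pairing on slum share may remove more. The documents quantify neither, so the single-visit figures are a guide, not the error of the difference-in-differences contrast.

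**The choice of governing method can be left to an analysis plan.** That is fair for ranking the methods. It does not excuse naming, in the article itself, between-arm tests that are invalid for the design.

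**Conclusion.** The concern holds in a limited form. As written, means are assigned only to methods that ignore the randomised unit. The household-segregation proportion has a cluster-adjusted method with an unadjusted chi-square beside it and no order between them.

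For an unadjusted household-level test at one visit, the true error is about 17% at the plan's design effect of 2. It is about 13.5% if that design effect belongs to 110 households per ward and about 79 are analysed. Either is well above twice the nominal 5%. Carrying these figures over to means, to group-level waste outcomes or to change from baseline is an assumption.

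Naming GEE does not by itself settle the matter. With four wards per arm, an uncorrected sandwich test still rejected about 14% in the simulation, whereas tests on ward summaries held about 5%.

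**What to change.** - Remove Student t, chi-square, rank tests on households, and factorial ANOVA without a ward term as between-arm inference. Keep means, medians and percentages as description.
- State that every between-arm comparison, of means as well as proportions, estimates the difference in change from baseline. Use either an analysis of ward-level summaries or a ward-clustered model with a small-sample correction suited to eight wards.
- Name which of these governs for each primary outcome, and say how mis-sorted waste is classed.
- For skewed outcomes, transform the data or analyse ward summaries; do not switch to a rank test on households.

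The cost is wording in the analysis text and no new data. Intervals will be wider, and the ward-level analysis has only 6 degrees of freedom unpaired or 3 paired, so power will be lower than the unadjusted tests would suggest.
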